# Efficacy of individualized homeopathic treatment and fluoxetine for moderate to severe depression in peri- and postmenopausal women (HOMDEP-MENOP): study protocol for a randomized, double-dummy, double-blind, placebo-controlled trial

**DOI:** 10.1186/1745-6215-14-105

**Published:** 2013-04-23

**Keywords:** Perimenopause, Postmenopause, Depression, Homeopathy, Fluoxetine, Hamilton Rating Scale for Depression, Beck Depression Inventory

## Abstract

**Background:**

The perimenopausal period refers to the interval when women’s menstrual cycles become irregular and is characterized by an increased risk of depressive symptoms. Use of homeopathy to treat depression is widespread but there is a lack of clinical trials about its efficacy in depression in peri- and postmenopausal women. Previous trials suggest that individualized homeopathic treatments improve depression. In classical homeopathy, an individually selected homeopathic remedy is prescribed after a complete case history of the patient. The aim of this study is to assess the efficacy and safety of the homeopathic individualized treatment versus placebo or fluoxetine in peri- and postmenopausal women with moderate to severe depression.

**Methods/design:**

A randomized, placebo-controlled, double-blind, double-dummy, three-arm trial with a six-week follow-up study was designed. The study will be conducted in a public research hospital in Mexico City (Juárez de México Hospital) in the outpatient service of homeopathy. One hundred eighty nine peri- and postmenopausal women diagnosed with major depression according to the Diagnostic and Statistical Manual of Mental Disorders, 4th edition (moderate to severe intensity) will be included. The primary outcome is change in the mean total score among groups on the 17-item Hamilton Rating Scale for Depression after the fourth and sixth week of treatment. Secondary outcomes are: Beck Depression Inventory change in mean score, Greene’s Scale change in mean score, response and remission rates and safety. Efficacy data will be analyzed in the intention-to-treat population. To determine differences in the primary and secondary outcomes among groups at baseline and weeks four and six, data will be analyzed by analysis of variance for independent measures with the Bonferroni *post-hoc* test.

**Discussion:**

This study is the first trial of classical homeopathy that will evaluate the efficacy of homeopathic individualized treatment using C-potencies versus placebo or fluoxetine in peri- and postmenopausal women with moderate to severe depression. It is an attempt to deal with the obstacles of homeopathic research due to the need for individual prescriptions in one of the most common psychiatric diseases.

**Trial registration:**

ClinicalTrials.gov Identifier: NCT01635218.

## Background

Major depressive disorder (MDD) is the fourth most disabling medical condition worldwide and it is expected to be ranked second by the year 2020 [1,2]. It is typically recurrent and often chronic [3,4]. MDD is associated with high health care costs [5]. Women are approximately twice as likely to develop MDD as men [4,6]. The perimenopausal period refers to the interval when women’s menstrual cycles become irregular, which generally occurs above the age of 40. Transition to menopause has long been considered a period of increased risk for depressive symptoms, as was demonstrated in the Harvard Study of Moods and Cycles, a population-based prospective study that examined the association between lifetime history of major depression and the decline in ovarian function [6]. According to the Stages of Reproductive Aging Workshop (STRAW), transition to menopause is the period that precedes menopause and it is characterized by variations in cycle length (>7 days different from baseline or ≥2 skipped cycles and an interval of amenorrhea ≥60 days) [7]. The postmenopausal stage is the period that continues after 12 months or more of amenorrhea. Depressive symptoms increase during the transition to menopause [8]. A significant inverse association of follicle stimulating hormone (FSH) with depressive symptoms provides strong corroborating evidence that the changing hormonal milieu contributes to dysphoric mood in this transition period [9]. With menopause, seric levels of FSH usually exceed 40 mU/ml although, given the variability of individual hormone levels, the determination of menopausal status is generally made by clinical history rather than laboratory parameters. Furthermore, other hormones also change their serum concentrations. The decline in estrogen levels that is associated with menopause results in a wide range of symptoms, which include vasomotor symptoms (hot flushes and night sweats) [10].

The Hamilton Rating Scale of Depression (HRSD) and the Beck Depression Inventory (BDI) are two well-known standardized scales to assess depression severity used in trials worldwide. The Greene Climacteric Scale (GS) is also a standardized scale used in the Mexican population. It is intended specifically to be a brief and standard measure of core climacteric symptoms or complaints to be used for comparative and replicative purposes across different types of studies whether they are medical, psychological, sociological or epidemiological in nature. Three separate sub-scales measure vasomotor symptoms, somatic symptoms, psychological symptoms, and an additional probe is related to sexual function. Psychological symptoms can be further sub-divided to measure anxiety and depression [11,12].

Meta-analyses of antidepressant medications have reported only modest benefits over placebo treatment and, when unpublished trial data are included, the benefit falls below accepted criteria for clinical significance [13,14]. Specifically, a meta-analysis of clinical trial data submitted to the US Food and Drug Administration (FDA) revealed a mean drug-placebo difference in improvement scores of 1.8 points on the HRSD [15], whereas the National Institute for Clinical Excellence (NICE) used a drug-placebo difference of three points as a criterion for clinical significance when establishing guidelines for the treatment of depression in the UK. Antidepressants may be effective for severely depressed patients, but not for moderately depressed ones. Moreover, only about 50% of patients with MDD show a response (>50% reduction in baseline symptoms) and only about one in three attain remission (virtual absence of symptoms) within the first eight weeks of treatment [4,16-18].

Homeopathy is one of the most frequently used and controversial systems of medicine. It is based on the ‘principle of similars’; highly diluted preparations of substances that cause symptoms in healthy individuals are used to stimulate healing in patients who have similar symptoms when ill [19]. When a single homeopathic remedy is selected based on a patient’s symptoms picture, it is called ‘classical’ homeopathy [20]. In classical homeopathy, the treatment consists of two main elements: the case history and the prescription of an individually selected homeopathic remedy. The purpose of the homeopathic case history is to ascertain the totality of signs and symptoms of each patient, enabling the selection of an individualized homeopathic medicine [21].

Homeopathic medicines are produced through sequential agitated dilutions in Decimal (D), Centesimal (C) or Quinquagintamillesimal (Q or LM) potencies [21]. C-potencies are prepared by diluting a drop of a parent substance in 99 drops of ethanol followed by agitation of the solution (1 C). This procedure is repeated in consecutive agitated dilutions (2 C, 3 C, 4 C, and so on). Generally, high potencies are prescribed for mental symptoms.

Use of homeopathy to treat psychiatric and menopausal problems is widespread, and the need for more high-quality controlled trials has been identified [22,23]. Meta-analyses and systematic reviews have drawn mixed conclusions as to whether homeopathy is more effective than placebo in general medicine [20,24-28]. The database on studies of homeopathy and placebo in psychiatry is very limited, but results do not preclude the possibility of some benefit. Homeopathy efficacy was found for fibromyalgia and chronic fatigue syndrome, for example [22].

Bordet *et al.* conducted a multi-national prospective non-comparative observational study of homeopathic treatments for hot flushes and suggest that further investigation is justified [29]. Jacobs *et al.* conducted a randomized, double-blind study versus placebo performed over one year with 83 women suffering from breast cancer; patients received either individualized homeopathic treatment or a homeopathic complex or a placebo. This study did not show any significant difference between the three patient groups relative to the severity and frequency of hot flushes although there was a trend in the ‘individualized homeopathic treatment’ group during the first three months of the study [30]. Although depression is one of the most common symptoms in peri- and postmenopause, there is no controlled study of the homeopathic use of individualized treatment in depressive disorders in women at this stage.

Recently, results from a randomized, controlled, double-blind trial indicated that individualized homeopathic Q-potencies were non-inferior to the antidepressant fluoxetine in a sample of patients with moderate to severe depression [21,31]. Responder rates (defined as a decrease of at least 50% from baseline on the Montgomery and Asberg Depression Rating Scale) were higher (homeopathy 84.6%, fluoxetine 82.8%) than those usually found for antidepressants in clinical trials (43% to 75%) [21,31]. However, the efficacy of the individualized homeopathic C-potencies for peri- and postmenopausal women with depression has not been investigated.

### Aims

The primary aim of the study is to assess the efficacy of individualized homeopathic treatment (IHT) versus fluoxetine and placebo, and fluoxetine versus placebo in peri- and postmenopausal women with moderate to severe depression scored by the 17-item HRSD.

Secondary aims are: (1) to assess the efficacy of IHT versus fluoxetine and placebo, and fluoxetine versus placebo using the BDI and GS’s score; and (2) to determine the safety of IHT versus fluoxetine and placebo, and fluoxetine versus placebo in peri- and postmenopausal women with moderate to severe depression.

## Methods/design

### Study design

The study will be a randomized, placebo-controlled, double-blind, double-dummy, three-arm parallel, superiority trial with a six-week study duration.

### Study setting

The study will be conducted in a public, academic and research hospital in Mexico City, the Juárez de México Hospital (JMH), which belongs to the Ministry of Health (MoH), the central authority in charge of health policies and design programs. The MoH provides health care to people without social security. JMH is an academic specialized hospital. Homeopathy is part of the National Health System regularized by the MoH. The outpatient service of homeopathy was established in JMH in 2004 and provides health care for climacteric stage women daily.

### Participant recruitment

The recruitment methods will include advertisements through the internet, local media and community groups, and liaisons with general practitioners, gynecologists, psychologists and allied health professionals. Posters with information about the study protocol will be posted at the study site; brochures will be distributed among the hospital population. Participants are currently being recruited starting in March 2012. The study is planned to end in December 2013.

### Eligibility criteria

The entry criteria for the study will be: (1) 40 to 65 years of age; (2) diagnosis of major depression according to the Diagnostic and Statistical Manual of Mental Disorders, 4th edition (DSM-IV); (3) moderate to severe depression according to the 17-item HRSD (14 to 24 score); (4) no current use of homeopathic treatment for depression or antidepressants or anxiolytic drugs for three months prior to study entry; (5) not taking psychotherapy for at least three months before screening; (6) no use of estrogens or other medications known to affect ovarian function for at least three months before screening; (7) early transition to menopause, defined by a change in cycle length of seven days or longer in either direction from the participant’s own baseline for at least two cycles; or late transition to menopause, defined as three to eleven months of amenorrhea; (8) postmenopausal stage defined by 12 months or more of amenorrhea; and (9) capability and willingness to give informed consent and to comply with the study procedures.

Exclusion criteria include: (1) pregnancy or breastfeeding; (2) other psychiatric disorders different from moderate to severe depression (severe depression, schizophrenia, psychotic disorders, bipolar affective disorders, suicide attempt, and so on); (3) alcohol or other substance abuse; (4) known allergy to fluoxetine; and (5) cancer or hepatic diseases.

### Types of interventions

After inclusion, patients will be randomly assigned to either one of three groups illustrated in Figure 1: (1) IHT plus fluoxetine dummy-loaded; (2) fluoxetine (20 mg/day) plus IHT dummy-loaded; and (3) fluoxetine placebo plus IHT placebo.

**Figure 1 F1:**
[figure not shown]
Flow chart of the study groups.

The selection of the individualized remedy will be carried out after the case history by a certified medical doctor, specialized in homeopathy with 18 years’ experience in classical homeopathy. The case history will be based on Hahnemann’s methodology described in paragraphs 83 to 104 of Organon of Medicine, 6th edition. A complete medical history with clinical examination will also be done. All patients will have a full homeopathic case-taking including the collection of all the facts pertaining to the patient which may help in determining the totality of the symptomatology: past and present physical and emotional symptoms, family environment since childhood, stressful life events, marital satisfaction. The symptoms will be organized by hierarchy: mental, general and physical. In the first place, the strategy to choose the individualized remedy will be based on the most characteristic and clear mental symptoms. Secondly, general symptoms will be taken into account. A computerized version of the Synthesis Homeopathic Repertory 9.1 (Radar version 10) will be used to facilitate the prescription. Only one remedy will be prescribed at a time but it could be changed at every follow-up according to the patient’s symptoms.

C-potencies will be provided by Laboratorio Similia (Mexico City) and are manufactured according to the Mexican Homeopathic Pharmacopoeia and Hahnemann’s methodology. Each individualized homeopathic remedy will be prescribed in C-potencies (Appendix 1). Higher initial potencies will be tried, ranging from 30 to 200 C. The factors that influence the selection of the potency will include: clarity of mental symptoms, patient’s vitality and sensitivity, nature and kingdom (source) of medicine, chronicity and presence of any pathological disorder. A single dose of the individualized homeopathic remedy selected will be dissolved in a 60 ml bottle of 30% alcohol-distilled water. Patients will receive 15 drops PO two times per day following agitation for 10 days, plus fluoxetine-dummy loaded prescribed PO daily. A double-dummy technique with matching placebos for each active treatment will be applied, thus both placebos will seem identical to their corresponding *verum* formulations. Follow-up will be at weeks four and six after the first clinical interview.

Patients in the fluoxetine group will receive 20 mg/day PO plus IHT-dummy loaded. IHT-dummy loaded will be repeated at week four. Capsules of a generic fluoxetine will be provided by Laboratorio Similia (Mexico City). Placebo capsules will contain sucrose micro globules. Homeopathic placebo bottles will be filled with the same amount of 30% alcohol-distilled water. Patients will receive 15 drops PO of this solution two times per day following agitation for 10 days. The homeopathic placebo will be repeated at week four.

The third group will receive both fluoxetine and IHT placebos, as previously described.

### Criteria for discontinuing or modifying allocated interventions

Some adverse effects have been observed during fluoxetine treatment: lack of interest in sex, sexual dysfunction, nausea, insomnia, somnolence, anorexia, anxiety, asthenia, tremor, allergic skin reactions. If they are serious and/or result in interruption of treatment, they will be reported as adverse events.

During the IHT participants could have one of these reactions: (1) temporary intensification of symptoms before the condition improves, which is named ‘homeopathic aggravation.’ If it occurs at all it is usually mild and simply an indication that the body is resolving the problem in a natural and healthy way. If aggravation is too distressing it will be lessened by using frequent doses of the same remedy in a lower potency; (2) improving symptoms without aggravation; and (3) the appearance of new symptoms different from those on which the prescription was based. They will be reported as adverse events. They are rarely serious, but in that case, the IHT will be stopped. If the participant experiences the same symptoms of the remedy, the corresponding antidote will be prescribed.

Each participant will receive a report form on which to write daily any adverse event observed during the trial duration. Study participants will be retained in the trial whenever possible to enable follow-up data collection and prevent missing data.

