### Outcomes

The primary efficacy outcome is the change from baseline in mean total depression score using the 17-item version of the HRSD at weeks four and six. The severity of symptoms will be assessed by a blinded investigator (clinical psychologist) from the JMH. The secondary outcomes are: change from baseline in mean total depression score using BDI (a self-reported scale) at weeks four and six; change from baseline in mean total score of GS at weeks four and six; responder rates (response rate: decrease of 50% or more from baseline score; remission rate: HRSD ≤7). The number and severity of all adverse events and homeopathic aggravations during the study period and 15 days after the final dose will be collected to determine the safety of fluoxetine and homeopathic medicines. An adverse event will be defined as any untoward medical occurrence in a subject without regard to the possibility of a causal relationship. Adverse events will be collected after participants have given consent and enrolled in the study and 15 days after study completion.

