### Statistical analysis

All patients under randomization will be included in the primary efficacy population (intention-to-treat population), regardless whether or not they adhered to the treatment protocol or provided complete data sets. Only patients who withdraw their consent to use their personal data will be excluded from the analysis. The flow of participants through the trial will be presented in a Consolidate Standards of Reporting Trials (CONSORT) diagram.

First, the three groups will be compared in order to verify that there are no significant differences among them at baseline to confirm they are comparable after randomization. Demographic characteristics will be summarized using means and standard deviation for continuous data (that is, age) and relative frequencies for qualitative data (that is, marital status, comorbidities). The baseline demographic characteristics among groups will be compared with the use of the chi square test or by one-way independent measures of analysis of variance (ANOVA) as required.

We will compare: (1) IHT versus placebo; (2) fluoxetine versus placebo; and (3) IHT versus fluoxetine. The main statistical analysis will compare primary and secondary outcome measurements among groups at weeks four and six. The primary outcome (change in mean HRSD score) and secondary outcomes (change in mean BDI and GS scores) among groups at baseline and weeks four and six, will be analyzed by one-way ANOVA to provide a statistical test of whether or not the means of the three groups are all equal. The statistically significant one-way ANOVA result (*P* <0.05) suggests rejecting the global null hypothesis H_0_ (that the means are the same across IHT, fluoxetine and placebo groups). The Bonferroni *post-hoc* test will be used to determine which means differ among the groups. Responder rates will be compared among the groups using the chi square test. Statistical significance will be set at *P* <0.05 level for all analysis. Missing data will be handled by sensitivity analysis.

All patients who received at least one dose of the study drugs will be considered in the safety analysis. Adverse events will be translated to Medical Dictionary for Regulatory Activities terms (MeDRa terms), quantified and compared among the groups using the chi square test. Homeopathic aggravation will be compared among the groups also using the chi square test.

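### The reporting threshold for listed fluoxetine effects conflicts with the protocol's own adverse-event definition and, if followed, would bias the safety comparison in fluoxetine's favour

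*Protocol article*

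**What the plan says.** The section on criteria for discontinuing or modifying allocated interventions names ten effects seen with fluoxetine: "lack of interest in sex, sexual dysfunction, nausea, insomnia, somnolence, anorexia, anxiety, asthenia, tremor, allergic skin reactions". Its reporting rule for them is conditional: "If they are serious and/or result in interruption of treatment, they will be reported as adverse events".

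The next paragraph lists three possible reactions during IHT. The first is temporary aggravation. The other two are "2) improving symptoms without aggravation; and (3) the appearance of new symptoms different from those on which the prescription was based". The rule that follows has no condition: "They will be reported as adverse events. They are rarely serious, but in that case, the IHT will be stopped".

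The same section ends with a daily diary for all participants: "Each participant will receive a report form on which to write daily any adverse event observed during the trial duration".

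The Outcomes section gives the general definition: "An adverse event will be defined as any untoward medical occurrence in a subject without regard to the possibility of a causal relationship". It adds that the number and severity of all adverse events, and of homeopathic aggravations, will be collected.

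Under Statistical analysis, adverse events are to be coded, then "quantified and compared among the groups using the chi square test". Aggravation gets a separate chi-square comparison. Safety across the three arms is the second of the secondary aims.

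**The concern.** Read together, the sections set two thresholds for what counts as an adverse event. An effect on the fluoxetine list counts if it is serious or interrupts treatment. A reaction on the IHT list, at least a new symptom, counts without any such condition. The general definition has no threshold at all.

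Most effects on the fluoxetine list, such as nausea, insomnia or somnolence, are commonly non-serious, and they are the events on which fluoxetine would be expected to differ from placebo. A rule that drops the non-serious ones removes much of the signal that the safety comparison exists to detect.

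The two lists also overlap. New insomnia in a blinded patient could be a listed fluoxetine effect, subject to the threshold, or a new symptom, which is not. The text does not say which rule prevails, so the count may depend on what the recorder guesses the patient is taking.

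**Working it through.** **Step 1. The statements side by side.**

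| Event | Discontinuation section | Outcomes definition |
|---|---|---|
| Non-serious nausea, treatment continues | Does not meet the reporting condition | Adverse event |
| New symptom, read as an IHT reaction | Reported, no threshold | Adverse event if untoward |
| Improvement without aggravation | Reported on a literal reading | Not untoward, so not an adverse event |
| Aggravation | Reported on a literal reading | Named alongside adverse events and tested separately |

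The first row is a direct conflict. The third is a conflict only on the literal reading. The fourth leaves open whether aggravation enters one comparison or two.

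**Step 2. Direction when the rule is applied blind.** Participants, the homeopathic doctor, the psychologist and the statistician are blinded, so take the rule as working by event type in all arms. Let q be the true incidence of listed effects and s the share that are serious or interrupt treatment. The recorded incidence is about q × s in each arm, and the difference between arms shrinks by the factor s. The loss in absolute terms is greatest in the arm with the largest q, expected to be fluoxetine.

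**Step 3. Illustration of size.** The document states no event rates, so there is no figure of its own to reproduce. Inputs from the document are 63 patients per group (Sample size calculation) and significance at 0.05 (Statistical analysis). All event rates are assumptions. The comparison shown is fluoxetine versus placebo, two-sided, by normal approximation:

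power = Φ[(|p1 − p2| − 1.96 × SE0) / SE1], with SE0 = √[2p̄(1 − p̄)/n] and SE1 = √{[p1(1 − p1) + p2(1 − p2)]/n}.

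| Recorded rates, fluoxetine vs placebo | SE0 | SE1 | Argument of Φ | Power |
|---|---|---|---|---|
| All events: 40% vs 20% | 0.0816 | 0.0797 | (0.20 − 0.1600)/0.0797 = 0.50 | 0.69 |
| s = 1/5: 8% vs 4% | 0.0423 | 0.0422 | (0.04 − 0.0829)/0.0422 = −1.02 | 0.15 |
| s = 1/10: 4% vs 2% | 0.0304 | 0.0303 | (0.02 − 0.0596)/0.0303 = −1.30 | 0.10 |

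**Step 4. A wider range that keeps unlisted events.** Add unlisted events at 10% in each arm, independent of the listed ones and always recorded. Recorded incidence is then 1 − (1 − q × s)(1 − 0.10). For q of 40 vs 20%, 50 vs 25% and 60 vs 30%, the difference with full reporting is 18 to 27 points, with power 55% to 87%. With s from 5% to 20%, the recorded difference is about 1 to 5 points, with power 4% to 12%. For example, 40 vs 20% with s = 10% gives 1 − 0.96 × 0.90 = 13.6% against 1 − 0.98 × 0.90 = 11.8%. Figures near or below 5% arise because the formula counts rejections in one direction only; they mean essentially no power.

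**The case against.** The strongest reply is that the conditional sentence is not a data-collection rule. It stands in a section on discontinuing or modifying treatment, and nowhere does it say that milder effects go unrecorded. The text that does concern collection, in Outcomes, Data collection and the diary sentence, is unconditional, and collecting severity for all events would make little sense if only serious or interrupting ones counted. This stands to a degree: *only if* is implied, not written. But a conditional reporting sentence has no function if every such event is reported anyway, so site staff are left with two rules.

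Second, a reader might infer that improvement is always reported as an adverse event on IHT. The wording permits this but does not establish it. The rule follows directly on the item about new symptoms, and the remark that these reactions are rarely serious does not fit "improving symptoms without aggravation". The narrower reading, new symptoms alone, is at least as sensible. It still leaves new symptoms without a threshold and the listed fluoxetine effects with one.

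Third, a reader might infer that events are filtered in the fluoxetine arm alone. If they were, equal true incidence of 30% or 50% in all arms would make the three-group test reject in 34% to 100% of trials, under the assumption that 5% to 20% of listed effects pass the threshold and that half to all of the fluoxetine-arm events are of listed types. The documents do not support this as the general case, because blinded staff cannot apply a rule by arm. One opening remains: under Allocation, the pharmacist may tell the homeopathic doctor what a patient is taking when adverse events occur.

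Fourth, blinding and the overlap of the lists may mean that little is lost, since in any arm a new complaint could be recorded as a new symptom. That is possible, but it depends on the recorder and not on the protocol.

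Finally, all rates in the illustration are assumed, and the normal approximation is rough at 4% vs 2%, where about 2.5 and 1.3 patients are expected (63 × 0.04 and 63 × 0.02). Both points are fair.

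**Conclusion.** The inconsistency is real and should be fixed. The discontinuation section and the Outcomes definition give different answers for non-serious effects on the fluoxetine list, and the resulting counts feed a between-group test for a stated secondary aim.

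The bias is conditional: it arises to the extent that the discontinuation section governs reporting. In that case non-serious fluoxetine effects are under-counted and the fluoxetine-placebo difference shrinks. Any additional counting of IHT reactions in patients believed to be on IHT would push the IHT-fluoxetine contrast the same way. The distortions do not offset each other; in that contrast both favour fluoxetine.

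The size cannot be determined from the document. The fall in power from about 69% to 10–15% rests on assumed incidences of 40% and 20%, on one in ten to one in five events passing the threshold, and on strict application of it. It shows what the rule could do, not what it did. Nothing in the documents quantifies an excess of events recorded under IHT. The primary outcome, its analysis and the sample size are untouched.

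**What to change.** Reconcile the three sections as follows.

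- Delete the reporting threshold for the listed fluoxetine effects. Apply the Outcomes definition to every patient in every arm, taking events from the daily form.
- Record seriousness and interruption of treatment as separate fields on each event, so that a restricted tabulation remains possible alongside the full one.
- State that improvement is not an adverse event, and make clear which IHT reactions the reporting sentence covers.
- State whether homeopathic aggravation counts within adverse events or only in its own comparison, and that it is assessed blind in all three arms.

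This concerns reporting and counting only. The rules for modifying or stopping treatment are not part of the change.

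The cost is protocol and case-report-form wording and somewhat more event coding. Participants already complete a daily form, so events since recruitment began in March 2012 should be recoverable from it. The rule should be settled before events are coded and before the treatment code is broken.
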